### Statistical Analysis

Power calculation was completed using the G-Power software v.3.1 (78) for the primary end point change in insulin sensitivity. The power calculation was based on the difference in insulin sensitivity in the meal tolerance tests conducted in the morning and in the evening in subjects with IFG/IGT in our previous study (21). For the sample size of 30 study participants, the planned study was powered to detect an effect size of 0.53 at a significance level of 0.05 and statistical power of 80%. The allocation of subjects to study arms was performed by matching for age and BMI using a minimization method and the MinimPy software (79).

Statistical analyses were performed with the SPSS 20.0 software (SPSS, Chicago, IL, United States). To estimate the effects of the dietary interventions on anthropometrical and metabolic parameters, linear mixed-effect models were applied with treatment, period, and residual effect as fixed factors and the study participants as a random factor. Sampling distribution was analyzed by Shapiro–Wilk test. Not normally distributed data were log-transformed before analysis. For NEFA, glucose, and meal-induced hormone secretion, areas under the curve (AUC) and incremental AUC (after subtraction of the baseline area, iAUC) were determined by trapezoidal method. Insulin sensitivity and insulin secretion indices in OGTT were calculated as described (80). For the comparison of two groups, paired Student's *t*-test or Wilcoxon test was performed depending on the distribution of data. A *p*-value < 0.05 was considered statistically significant. For multiple testing, false discovery rate correction was applied.

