## Materials and Methods

### Study Design

The study named “ChronoFast” is a 10 week randomized, controlled cross-over clinical trial that will be performed in a German population of female subjects with overweight or obesity. The study will consist of two 2 week dietary intervention periods: (1) early TRE and (2) late TRE. After a 4 week long run-in period, the participants will be randomly assigned to either 2 weeks of eTRE or 2 weeks of lTRE as their first intervention. The first phase of intervention will be separated by a 2 week washout period from the second phase of TRE intervention that will be the opposite of the first intervention (Figure 1). The duration of the run-in phase, and the washout and intervention phases were chosen to exclude the effect of monthly ovarian cycle in women (both intervention phases will be approximately at the same phase during both interventions). Previous data of our and other groups show that change in dietary pattern for 2 weeks is sufficient to induce strong changes in metabolic state (55, 58, 66). Furthermore, the short 2 week duration of TRE interventions will make the rigorous monitoring of food intake and physical activity more feasible and will allow for the achievement of minimal variation in body weight.

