### Primary and Secondary Outcomes

The primary outcome was the insulin sensitivity assessed using Matsuda index in OGTT (77). Secondary outcomes included body weight, BMI and body fat content, fasting glucose, homeostasis model assessment of insulin resistance (HOMA-IR), indices of insulin secretion and beta-cell function assessed in OGTT, mean daily glucose and daily glycemic variation indices assessed in CGM, levels of hormones related to glucose metabolism, hormones of appetite regulation, adipokines and inflammatory markers, blood lipid and liver enzyme levels, systolic and diastolic blood pressures, satiety and hunger scores, sleep quality and duration, physical activity, social and economic decision behaviors, dietary calorie intake, composition, timing, and eating window duration. The main exploratory outcome was the activity of signaling pathways and expression of metabolic and inflammatory genes in adipose tissue and blood monocytes.

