The cross-over design is another very essential strength of the ChronoFast trial protocol, which will allow for the comparison of cardiometabolic effects of eTRE vs. lTRE directly in the same study subjects. Until now, only one cross-over trial that compared the effects of eTRE and lTRE has been published (58), which was accompanied by manifested weight loss after both interventions and, possibly due to this reason, observed no difference in the improvement of glucose and lipid levels between two dietary patterns. Notably, the 10 week study in the United Kingdom, which also aims to compare the metabolic effects of eTRE and lTRE on adults with increased type 2 diabetes risk, is currently ongoing (82). However, this study uses a three-arm parallel study design, whereas the ChronoFast study has a cross-over design, which removes variability between participants because each study subject acts as his own control.

Notably, a range of published TRE studies was conducted only with male participants, especially when time frames are short, as female participants tend to show cyclic changes in body weight and behavior owing to the female cycle. Thus, working with solely female participants is also a strength of this study. Because of the 4 week run-in phase and the detailed recording of baseline characteristics before each intervention, confounding factors will be eliminated.

The last objective of the ChronoFast study is assessment and comparison of molecular mechanisms induced by eTRE and lTRE in adipose tissue and blood monocytes. Numerous molecular mechanisms underlying the metabolic effects of TRE are intensively investigated in animal studies (45, 46, 83). Postprandial increase in various nutrients, such as glucose, lipids, and amino acids, affects both glucose and lipid metabolism and circadian clock pathways *via* key intracellular metabolic sensors such as SIRT1, mTOR, S6K, AMPK, PPARs, RORs, and Rev-Erbs (84). Notably, insulin (and possibly other meal-induced hormones) can directly entrain the circadian clock in liver and adipose tissue and in this way additionally affect metabolic outcomes (85, 86). The elegant study of Mukherji et al. (83) confirmed a central role of PPARα, Rev-Erbα, and CREB in circadian and metabolic changes induced by shifting of feeding time. However, most of these mechanisms were described in rodents and require intensive investigation in clinical settings to prove feasibility, safety, and effectiveness.

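### Allocation is minimised on age and BMI, but the listed mixed model omits both; if its residual effect is a carry-over term with one response per period, this costs some precision

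*Protocol article*

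**What the plan says.** Under Statistical Analysis the article describes allocation to sequence: "The allocation of subjects to study arms was performed by matching for age and BMI using a minimization method". The same section gives the model: "linear mixed-effect models were applied with treatment, period, and residual effect as fixed factors and the study participants as a random factor". Neither age nor BMI appears in it.

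Study Design sets out two sequences and two periods: "The first phase of intervention will be separated by a 2 week washout period from the second phase of TRE intervention". The primary outcome is a Matsuda index (Primary and Secondary Outcomes: "The primary outcome was the insulin sensitivity assessed using Matsuda index in OGTT"). The sentence on power, however, names the change in insulin sensitivity as the primary end point, and OGTTs are done before and after each intervention (Table 1, visits 1–4).

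Two statements point to a within-woman comparison. Statistical Analysis also names paired tests: "For the comparison of two groups, paired Student's *t*-test or Wilcoxon test was performed depending on the distribution of data". The Discussion justifies the cross-over as a design "which removes variability between participants because each study subject acts as his own control". On size, the article says: "For the sample size of 30 study participants, the planned study was powered to detect an effect size of 0.53", with 80% power at the 0.05 level.

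The article does not say how the residual effect is coded or which visits enter the model.

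**The concern.** Factors used in minimisation are normally kept in the analysis model. Balancing on them reduces the true variability of a between-group contrast, but a model that omits them still counts their variance as error. In a cross-over the usual reply is that factors fixed within a woman cancel. That reply holds only if the treatment estimate is a within-woman contrast. A carry-over term in a two-by-two cross-over removes exactly that property. If the listed model is fitted in that form, the primary comparison gives away precision that the allocation has already provided.

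**Working it through.** **Inputs.** From the article: N = 30, effect size 0.53, alpha 0.05, power 80%, two sequences by two periods, and the model terms above. Assumed, because the article does not give them: 15 women per sequence; outcome SD 1; within-woman correlation ρ of 0.5 to 0.8; share of outcome variance explained by age and BMI, R², of 0.1, 0.2 or 0.3; a two-sided test.

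**1. The plan's own figure.** For a paired t-test with n = 30 and dz = 0.53, the noncentrality is 0.53 × √30 = 2.90 on 29 df. Two-sided power is 80.1%, so the figure reproduces as a paired comparison. Two independent groups of 15 at d = 0.53 give 28.9%.

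**2. What the listed model estimates.** Let E-L be the sequence with eTRE first and L-E the sequence with lTRE first. Let μ be the intercept, π the period effect, τ the treatment difference and λ the carry-over difference. The four cell means are:

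| Sequence | Period 1 | Period 2 |
|---|---|---|
| E-L | μ + τ/2 | μ + π − τ/2 + λ/2 |
| L-E | μ − τ/2 | μ + π + τ/2 − λ/2 |

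Four parameters fit four means. The period-1 difference equals τ. The period-2 difference equals −τ + λ, so λ absorbs it and period 2 adds nothing on treatment. Generalised least squares confirms this: the weights on (period 1, period 2) are (1, 0) in one sequence and (−1, 0) in the other, at every ρ tried. Without the residual term, or with a sequence term in its place, the weights are (0.5, −0.5) and (−0.5, 0.5), which sum to zero within each woman.

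**3. Standard errors.**
- With carry-over, no covariates: √(2/15) = 0.365, whatever ρ is.
- With carry-over, age and BMI added: √(2(1 − R²)/15) = 0.346, 0.327 and 0.306 for R² = 0.1, 0.2 and 0.3, that is 5%, 11% and 16% smaller.
- Without carry-over: √(2(1 − ρ)/30) = 0.183, 0.141 and 0.115 for ρ = 0.5, 0.7 and 0.8. With complete data, adding age and BMI changes nothing.

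**4. Is the unadjusted standard error too large?** A simulation with 15 v 15 balanced on both factors and R² = 0.2 gave a model SE of 0.364 without the covariates, against a true sampling SD of 0.323. With the covariates the model SE was 0.325. Adjustment carried no material penalty at R² = 0.

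**5. Power at the difference implied by dz = 0.53.** That difference is 0.53 × √(2(1 − ρ)), which is 0.530 at ρ = 0.5 and 0.411 at ρ = 0.7. For a 15 v 15 comparison:

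| ρ | No covariates | R² = 0.1 | R² = 0.2 | R² = 0.3 |
|---|---|---|---|---|
| 0.5 | 28.9% | 31.5% | 34.7% | 38.8% |
| 0.7 | 19.2% | 20.8% | 22.9% | 25.5% |

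These use 28 df. Spending two df on the covariates lowers the adjusted figures by less than 0.2 percentage points.

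**6. Other layouts.** If all four visits enter as responses and carry-over covers visits 3 and 4, the weights within a woman at ρ = 0.5 are −0.286, 0.571, 0.429 and −0.429. They sum to 0.285, against 1 in step 2. If carry-over is confined to visit 4, the weights are −0.333, 1, −0.333 and 0, with sum 0.334. Both contrasts are only partly between women, and the gain from adjustment is correspondingly smaller.

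**The case against.** The strongest reply is that the harm comes from the residual term and not from missing covariates. Drop the term and, with complete data, the point is empty; keep it and adjust, and power is still far below 80%. This stands. It makes the covariates a secondary repair, but they still help while the term remains.

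Second, the power sentence names change as the end point. If the response is post minus pre within each period, additive effects of age and BMI on the Matsuda level subtract out, even in a first-period comparison. This also stands. Some gain then remains only if age or BMI modifies the response, and the article gives no figure for that. The assumed R² values suit levels better than changes.

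Third, the article does not fix the coding of the residual effect, and it names paired tests that need neither factor. So a reader might infer that the primary analysis is certainly a between-group comparison. The text does not support that; it follows only under one reading, though that reading is a natural one for a residual effect in a cross-over model.

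Fourth, covariate lists are often left to the analysis plan. That is fair for unstated detail. Here, though, the article sets out the model's fixed factors, and the point concerns that stated list.

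A reader might also infer bias. None follows: with balanced allocation the omission leaves the estimate centred and errs towards too large a standard error.

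**Conclusion.** The point holds conditionally and is modest in size. If the residual effect is first-order carry-over with one response per period, omitting age and BMI leaves the standard error at 0.365 SD where 0.346 to 0.306 would do. This rests on 15 women per sequence and an assumed R² of 10–30%, for which the article gives no source. Under the other readings the gain shrinks or disappears.

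It would be wrong to conclude that adding the two factors rescues the primary analysis. With correlation 0.5 to 0.7, adjusted power is about 20–40%. The larger inconsistency is between the residual term on one side and the paired power figure and own-control rationale on the other.

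**What to change.** State how the residual effect is coded, which visits enter the model, and whether the response is the post-intervention value or the change. While a carry-over term stays in the model, add age and screening BMI as continuous fixed covariates, for the primary outcome and for the other outcomes analysed with that model. The cost is one line of text and two between-subject degrees of freedom, with no new data.

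Separately, reconsider the residual term in the primary model. Removing it restores the within-woman contrast on which the power figure rests (SE 0.183 to 0.115 at correlation 0.5 to 0.8). The covariates then make no difference when data are complete.

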#### Subcutaneous Adipose Tissue Biopsies and Blood Monocyte Collection

Subcutaneous adipose tissue biopsies were collected at visits 2 and 4 at the level of the umbilicus using a well-established technique (72). The skin was anesthetized with 1% lidocaine. A small incision was made, and 1 g of adipose tissue was removed under sterile conditions using a cutting needle biopsy handy (14 G Somatex™, Germany). SAT biopsies were collected immediately before OGTT and frozen in liquid nitrogen until further analyses. An RNA-Seq analysis of the SAT samples was performed to elucidate and compare signaling pathways affected in the adipose tissue by eTRE and lTRE and validated by quantitative real-time PCR.

Peripheral blood mononuclear cells were isolated from fasting EDTA blood using BD Vacutainer® CPTTM with an integrated FICOLL™-gradient (BD Biosciences, East Rutherford, NJ, USA). Blood monocytes were isolated from the peripheral blood mononuclear cell (PBMC) samples using whole-blood CD14 microbeads (Miltenyi Biotec, North Rhine-Westphalia, Germany) as described (73). The PBMC and monocyte samples were stored at −80°C until the analysis of inflammatory gene expression and BodyTime assay for the determination of TRE effects on internal circadian time (74).

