#### Questionnaires and Decision Behavior Tests

The chronotypes of the subjects were assessed using the Munich Chronotype Questionnaire (MCTQ) and the Horne-ÖstbergMorningness-Eveningness Questionnaire (MEQ).

Satiety and hunger scores were assessed using Visual Analog Scale (VAS) for (1) desire to eat, (2) hunger, (3) satiety, and (4) capacity to eat, as described previously (21). VAS surveys were completed once in the morning at 8:00 h and once in the evening at 20:00 h on the last day of each intervention (the day before visits 2 and 4).

Social and economic decision behaviors were assessed by computer tests together with the Barratt Impulsiveness Scale and the UCLA Loneliness Scale in cooperation with [name] (Dept. Decision Neuroscience and Nutrition, German Institute of Human Nutrition).

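### The period-adjusted model is described only for anthropometric and metabolic outcomes; on the natural reading, the decision tests and VAS scores are compared by paired tests that ignore period

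*Protocol article*

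**What the plan says.** The Statistical Analysis section of the protocol article describes two ways of comparing the diets.

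- A mixed model: "To estimate the effects of the dietary interventions on anthropometrical and metabolic parameters, linear mixed-effect models were applied with treatment, period, and residual effect" (all fixed, with participant as a random factor).
- A simple test: "For the comparison of two groups, paired Student's *t*-test or Wilcoxon test was performed depending on the distribution of data". No outcome is named, and there is no period term.

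Primary and Secondary Outcomes lists secondary outcomes that are neither anthropometric nor, in ordinary usage, metabolic: "satiety and hunger scores, sleep quality and duration, physical activity, social and economic decision behaviors". The decision outcomes are described as follows: "Social and economic decision behaviors were assessed by computer tests together with the Barratt Impulsiveness Scale and the UCLA Loneliness Scale". Table 1 marks both the decision tests and the VAS scores at Visits 2 and 4 only, that is, once at the end of each intervention (weeks 6 and 10). The PSQI, by contrast, is marked at pre-screening, screening and every visit, and the ActiGraph is also worn during run-in.

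Gene expression in adipose tissue and monocytes is the main exploratory outcome. The article says that RNA-Seq was done on the adipose samples and validated by PCR, but states no statistical test for it.

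**The concern.** In a two-period cross-over, anything that shifts all women between the first and second period (practice, familiarity, season, fatigue with the study) enters the eTRE-minus-lTRE difference with one sign in one sequence and the opposite sign in the other. A model with a period term removes it. A paired test does not: it treats the shift as noise between women, and when the sequences differ in size part of it stays in the estimate.

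The authors include period in the model for the outcomes they name, so they accept that it matters. The decision tests are where it is most plausible. They are computer tasks with no earlier session in Table 1, so any practice effect falls wholly between the two periods. The decision tests and the VAS also have no pre-intervention measurement, so a change score cannot absorb the shift. The risk is a missed difference between the diets on these outcomes or, with unequal sequences, a distorted one.

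**Working it through.** **Inputs from the article (Statistical Analysis).** N = 30, effect size 0.53, significance level 0.05, power 80%. Allocation is by minimisation on age and BMI; no sequence sizes are stated.

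**Assumed, because the article does not give them.** A period effect π from 0 to 1.0, in SDs of the within-woman difference; sequence sizes n1/n2 of 15/15, 16/14, 16/12 (28 completers) and 20/10. The 0.53 is the article's figure for the primary endpoint and is borrowed here only as a yardstick.

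**Step 1: the article's own figure.** A two-sided paired t-test with n = 30 and standardised difference 0.53 has noncentrality 0.53 × √30 = 2.903 on 29 df, which gives power 80.1%. The stated 80% is reproduced.

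**Step 2: model.** For woman i, the eTRE-minus-lTRE difference is D = τ + sπ + e, with SD(e) = 1 and s = +1 or −1 by sequence.

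- Paired test: the estimate is the mean of all D, with N − 1 df. Its bias is π(n1 − n2)/N. The expected sample variance of D is 1 + π²·[N/(N − 1)]·[1 − ((n1 − n2)/N)²].
- Period-adjusted test: the estimate is the average of the two sequence means, with standard error 0.5·√(1/n1 + 1/n2) in SD units and N − 2 df. π cancels.

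**Step 3: equal sequences, 15/15.** Adjusted: the standard error is 0.5·√(2/15) = 0.1826, noncentrality is 0.53/0.1826 = 2.903 on 28 df, and power is 80.0% for any π. Paired: the bias is zero, but at π = 0.5 the SD used by the test rises to √(1 + 0.25 × 30/29) = 1.122. The true variability of the mean does not rise, so the test is conservative. Simulated results:

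| π (SD) | Paired power | Adjusted power | Paired type I error |
|---|---|---|---|
| 0 | 80% | 80% | 5.0% |
| 0.25 | 78% | 80% | 4.4% |
| 0.5 | 73% | 80% | 2.9% |
| 0.75 | 63% | 80% | 1.5% |
| 1.0 | 50% | 80% | 0.6% |

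**Step 4: unequal sequences.** Bias for π = 0.5:

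- 16/14: 0.5 × 2/30 = 0.033 SD
- 16/12: 0.5 × 4/28 = 0.071 SD
- 20/10: 0.5 × 10/30 = 0.167 SD

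For π = 1.0 each figure doubles.

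At 16/12 the adjusted test has standard error 0.5·√(1/16 + 1/12) = 0.191, noncentrality 0.53/0.191 = 2.78 on 26 df, and power 76%. Paired power depends on the sign of the period effect:

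| π (SD), 16/12 | Bias opposes treatment effect | Bias favours treatment effect | Adjusted |
|---|---|---|---|
| 0.5 | about 55–56% | 81% | 76% |
| 1.0 | about 21–22% | 74% | 76% |

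Paired type I error at 16/12 is about 4% and 2% for these two period effects. Only with marked imbalance does it exceed 5%: at 20/10 it is about 10% for π = 0.5 and 17% for π = 1.0.

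**The case against.** The strongest objection is that the article does not assign these outcomes to the paired tests. The paired-test sentence names no outcome and could refer to before–after contrasts within a diet, and the mixed-model sentence does not say that it excludes anything else. A condensed article may also leave outcome-by-outcome assignment to a fuller plan. This stands in part: that these outcomes go to paired tests is an inference. It is a strong one for the decision tests and VAS, because with measurements only at Visits 2 and 4 no before–after contrast exists. The eTRE–lTRE comparison is the only one possible, and the article gives one method outside the metabolic model. The point also rests on what the article states (a model with a given scope and an order-blind alternative), not on something left out.

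Four stronger readings are tempting and are not supported.

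- A reader might infer that adipose gene expression is analysed without period. No test is stated for it. Although "Subcutaneous adipose tissue biopsies were collected at visits 2 and 4 at the level of the umbilicus", that does not show that an earlier biopsy affects a later one.
- A reader might extend the practice argument to every non-metabolic outcome. It fits the decision tests. It is weak for the PSQI and actigraphy, which begin before the interventions, and appetite hormones are naturally read as metabolic.
- A reader might take the low 16/12 power figures as the expected result. They hold only when the period bias opposes the treatment effect, and nothing in the article makes that sign more likely.
- A reader might infer that false positives rise. With equal or mildly unequal sequences the paired test is conservative.

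It is also fair to say that these are not the primary outcome and that 80% power was never claimed for them.

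**Conclusion.** The point holds in limited form. As written, the analysis section gives period adjustment to anthropometric and metabolic parameters and offers only an order-blind paired test besides. Following it would leave period effects in the decision-test and VAS comparisons, and less certainly in sleep and activity.

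The size rests on assumptions about the period effect and the sequence split. With equal sequences, the loss is about 2 percentage points of power at 0.25 SD, about 7 at 0.5 SD and about 30 at 1.0 SD, with no bias. With slightly unequal sequences the bias is small, 0.03 to 0.07 SD for a 0.5 SD period effect, and power can move either way. The loss is clear only for period effects of about 0.5 SD or more.

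The Matsuda index is a metabolic parameter, so the primary comparison is not affected if it is analysed with the stated mixed model. The change is still worth making, because adjustment costs almost nothing when there is no period effect (80.0% against 80.1% at 15/15).

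**What to change.** In Statistical Analysis, state that every eTRE–lTRE contrast on an outcome measured in both periods, including decision tests, VAS scores, sleep and activity, uses a linear mixed model with treatment and period as fixed effects and participant as a random effect. Where a rank-based test is needed, replace the signed-rank test with a rank-sum test between the two sequences on the within-woman differences, period 1 minus period 2. If the paired tests are kept for another purpose, name the comparisons they serve.

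The cost is one sentence or two and one degree of freedom (29 to 28 with 30 women). No new data are needed.

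### A fixed carry-over term in a two-period, two-sequence cross-over reduces the eTRE–lTRE estimate to a period-1 comparison of about 15 v 15 and undercuts the stated 80% power

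*Protocol article*

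**What the plan says.** The Study Design section describes a two-treatment, two-period, two-sequence cross-over: "the participants will be randomly assigned to either 2 weeks of eTRE or 2 weeks of lTRE as their first intervention", with the first phase "separated by a 2 week washout period from the second phase of TRE intervention that will be the opposite of the first intervention". The primary outcome is the Matsuda index from the OGTT (Primary and Secondary Outcomes).

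The Statistical Analysis section makes three statements that bear on how the two diets are compared:

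- Power is given "for the primary end point change in insulin sensitivity": 30 participants, "powered to detect an effect size of 0.53 at a significance level of 0.05 and statistical power of 80" per cent.
- For anthropometric and metabolic parameters, which include the Matsuda index, "linear mixed-effect models were applied with treatment, period, and residual effect as fixed factors and the study participants as a random factor".
- For comparing two groups, a paired t-test or a Wilcoxon test is used, depending on the distribution.

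The section does not say which of the last two is the primary analysis. The Discussion defends the cross-over on the ground that it "removes variability between participants because each study subject acts as his own control".

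**The concern.** A fixed residual effect in a cross-over ordinarily means carry-over: the effect of the previous treatment persisting into the next period. It cannot mean residual error, because that is not a fixed factor. In a design with only two sequences and two periods, carry-over cannot be fitted alongside treatment and period without giving up the within-participant treatment contrast. The period-2 data then serve to estimate carry-over and contribute nothing to the treatment effect.

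At stake is the primary comparison. The sample size was set for a within-woman test, and the Discussion presents the within-woman comparison as a central strength. The model as described would deliver neither.

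**Working it through.** **Inputs.** From the article: n = 30, effect size 0.53, significance level 0.05, power 80%, two sequences and two periods. Assumed: two-sided testing (not stated, but it reproduces the 80%); 15 women per sequence (sizes not stated; minimisation should give about this); equal variance σ² with correlation ρ between a woman's two values. The article does not give ρ, so a range is shown.

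**1. Reproduce the stated power.** Take 0.53 as the mean within-woman difference divided by its SD (dz). The noncentrality is 0.53 × √30 = 2.90. With 29 df, two-sided, power is **80.1%**. A one-sided test would give 88.3%. The power statement therefore matches a paired analysis of 30 women.

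**2. Count parameters.** Let τ be the treatment difference, π the period effect and λ the difference in carry-over. The four sequence-by-period means are:

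| Sequence | Period 1 | Period 2 |
|---|---|---|
| eTRE then lTRE | μ + τ/2 | μ + π − τ/2 + λ/2 |
| lTRE then eTRE | μ − τ/2 | μ + π + τ/2 − λ/2 |

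There are four means and four parameters, so the mean model is saturated. Subtracting within period 1 gives τ. In period 2, λ absorbs whatever is left. Generalised least squares confirms this: the weights for τ are +1 and −1 on the period-1 means and 0 on both period-2 means, at every ρ tried (0, 0.5, 0.7, 0.9). In one simulated data set the mixed model with carry-over gave 0.7547 (SE 0.326), identical to the period-1 mean difference. Without carry-over it gave 0.448 (SE 0.114). The random participant effect recovers nothing.

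**3. Variance of the treatment estimate.**

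- With carry-over: 2σ²/15 = 0.133σ², whatever ρ is.
- Without carry-over: 2σ²(1 − ρ)/30 = σ²(1 − ρ)/15.
- Ratio: 2/(1 − ρ).

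**4. Power for the same true difference.** In units of σ that difference is d = 0.53 × √(2(1 − ρ)). The test is a two-sample t-test, 15 v 15, 28 df, with noncentrality d/√(2/15).

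| ρ | d | Variance without carry-over (σ²) | Variance ratio | Power with carry-over |
|---|---|---|---|---|
| 0 | 0.750 | 0.067 | 2.0 | 51% |
| 0.3 | 0.627 | 0.047 | 2.9 | 38% |
| 0.5 | 0.530 | 0.033 | 4.0 | 29% |
| 0.7 | 0.411 | 0.020 | 6.7 | 19% |
| 0.9 | 0.237 | 0.007 | 20 | 10% |

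The model with treatment and period only (28 df) has 80.0% power at every ρ. With carry-over, the smallest difference detectable at 80% power is d = 1.06. At ρ = 0.5, 57 women per sequence would be needed.

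**5. Change from period baseline.** The saturation argument is the same with one change per period. Here ρ is the correlation between a woman's two changes, which is zero if all four visits are equally correlated. If 0.53 is defined on the changes, the ρ = 0 row applies: 51%.

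**6. All four visits modelled jointly.** With a separate mean for each visit, equal correlation across visits and carry-over kept, noncentrality is d divided by the square root of the variance (28 df). At ρ = 0.5:

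- Carry-over at visit 4 only: variance 0.089σ², noncentrality 0.53/√0.0889 = 1.78, power 40%.
- Carry-over equal at visits 3 and 4: variance 0.057σ², noncentrality 0.53/√0.0571 = 2.22, power 57%.

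Across ρ from 0 to 0.9 the two variants span about 37% to 68%.

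**7. Sequence term in place of previous treatment.** The treatment variance is 0.067, 0.033, 0.020 and 0.007σ² at ρ = 0, 0.5, 0.7 and 0.9, identical to the model without carry-over. Nothing is lost.

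**The case against.** The strongest defence is that the article does not force the damaging reading, and several parts of it stand.

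- *Coding is not given.* In this design carry-over is aliased with sequence and is often examined through a sequence term, which costs nothing (step 7). If that is what was meant, there is no power loss. However, the text names a residual effect, and previous treatment is its ordinary meaning.
- *The data modelled are not stated.* The OGTT is done at visits 1 to 4, so a joint four-visit fit is possible and would keep some within-woman information. But the listed factors include no visit effect, and even this fit reaches only about 37–68%.
- *A paired test is named in the same section.* It matches the power statement and keeps the within-woman comparison, though it ignores period. The article does not rank it against the mixed model.

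A reader might infer that the within-woman comparison is lost from the trial altogether. The documents do not support that, because the paired test is also there. A reader might also infer that modelling changes gives 29% power whatever ρ is. That figure defines 0.53 on the post-period values and then switches to changes. On that footing even the paired test of changes without carry-over has only 51% (dz = 0.53/√2 = 0.375), so the fall is from 51% to 29%, not from 80% to 29%.

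It may also be said that adjusting for carry-over is prudent. The 2-week washout already addresses carry-over by design, and the adjustment gives up the comparison that the design exists to make.

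**Conclusion.** The point holds in conditional form. If the residual effect is carry-over coded as previous treatment, and one value or one change per period is analysed, the stated model estimates the diet difference from period 1 alone. Power for the planned difference falls from 80% to about 51% at ρ = 0, 29% at 0.5 and 10% at 0.9. The assumptions are two-sided testing, about 15 women per sequence (imbalance would make it worse) and the assumed ρ. Every previous-treatment fit checked, including the four-visit ones, falls well short of 80%. The stated power is correct for a paired analysis; the fault is that the model does not match it. Because this concerns the primary comparison and the stated reason for the cross-over, it should be corrected before the data are analysed.

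**What to change.** Remove the previous-treatment residual effect from the mixed model. Keep treatment and period as fixed effects and participant as random. Name this model as the primary analysis of the Matsuda index, in place of the unranked paired test. If the term was meant as a sequence effect, say so.

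Rest the no-carry-over assumption on the 2-week washout. Support it with a descriptive comparison of visit 3 with visit 1 by sequence, using the OGTT, weight and fasting measurements already collected at those visits. That comparison must not be used to choose the model.

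The cost is a short change of wording and no new data. The one downside is that the estimate then assumes negligible differential carry-over, which the visit 3 values can help to judge but not prove.
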